#### 2.9 Clinical and radiographic evaluations of selected teeth

Clinical evaluations will be considered as the primary outcome and will be performed in a dental chair under the light of a reflector, using a clinical oral mirror and palpation of the affected tooth area. At the initial examination and at the 1, 3 and 6 month follow-up examinations, the following clinical data will be recorded: history of spontaneous pain indicative of apical periodontitis, presence of fistula or abscess, presence of gingival edema, and pathological mobility. As a secondary outcome, signs of radiolucency in the periapical region and pathological root resorption will be evaluated radiographically.

The clinical data collected in the initial examination and in the control of 1, 3 and 6 months after the treatment and the comparison of the initial radiograph for diagnosis with the radiographs taken in the control exams will be the basis for evaluating the success or failure of the endodontic therapy. The radiographs will be analyzed by two experienced and trained professionals, with the aid of a negatoscope. These professionals will not have any information regarding the treatment group to which each tooth belonged and, in case of doubts during the evaluation, a consensus between the examiners will be established.

The following criteria will be used to determine the success or failure of the proposed treatment, according to the work by Chan et al 15:

|                                  |                                                                                                                                                                                                                                                                                                                                                                                               |
|----------------------------------|-----------------------------------------------------------------------------------------------------------------------------------------------------------------------------------------------------------------------------------------------------------------------------------------------------------------------------------------------------------------------------------------------|

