| 1. Complete repair (=success)    | Clinically : absence of signs and symptoms.
radiographically : absence of pathological root resorption, normal width of the periodontal ligament space, absence of lesion development in the periapical region in cases of absence of lesion observed in the initial radiograph for diagnosis and total regression of the lesion when present at the beginning of treatment. |
| 2. Incomplete repair (= success) | Clinically : absence of signs and symptoms.
radiographically : absence of pathological root resorption and reduction in size of the lesion in the periapical region.                                                                                                                                                                                                         |
| 3. Failure to repair (= failure) | Clinically : signs and symptoms indicative of apical periodontitis in the acute phase.
radiographically : presence of pathological root resorption, lesion in the furcation/periapical region of unchanged size during the follow-up period, enlargement or development of a new radiographic lesion.                                                                        |

All radiographs will be standardized using adult periapical film (Kodak, Rochester, NY, USA) in the occlusal position (modified occlusal radiograph).

The same development time, intermediate wash, fixation and final wash at all evaluation times will be used to standardize radiography processing.

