## 2.10 Statistical analysis

For the primary outcome, the tooth will be the unit of analysis and the Kaplan-Meier test will be performed to estimate the survival rates of the included teeth. In addition, we performed an intention-to-treat (ITT) analysis, considering follow-up successes and failures. For comparison between the two groups, Student's t test or Mann-Whitney test will be performed, depending on the normality of the data. In addition, Poisson regression analyzes will be carried out, in order to allow the evaluation of the influence of some variables on the results. For all analyses, the significance value will be adjusted to 5%.

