### 3. Expected Results

Through the present work, we will be able to assess whether there will be a difference in effectiveness between the proposed treatments, as well as whether Guedes-Pinto paste in the NIET technique will present equal or better clinical and radiographic results when compared to the CTZ paste.

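### A non-inferiority trial with a 15% limit does not fix the success definition, visit or comparison that decides it, and runs every analysis at 5%

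*Protocol*

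**What the plan says.** - **Design and limit.** Protocol 2.2 declares a two-arm, 1:1 non-inferiority trial. Protocol 2.4 gives a limit of 15%, 80% power, a 5% significance level (sidedness not stated) and an assumed 12-month success rate of 86.4% for CTZ. The enrolled size is 60 teeth per group.
- **Primary outcome.** Protocol 2.9: "Clinical evaluations will be considered as the primary outcome". The timing is "At the initial examination and at the 1, 3 and 6 month follow-up examinations, the following clinical data will be recorded", and the items are "history of spontaneous pain indicative of apical periodontitis, presence of fistula or abscess, presence of gingival edema, and pathological mobility". No visit is marked as primary. Radiolucency and pathological root resorption are named as the secondary outcome.
- **Success rule.** The same section then says "The following criteria will be used to determine the success or failure of the proposed treatment". The table that follows requires, for success, the clinical condition "absence of signs and symptoms" together with radiographic conditions.
- **Analysis.** Protocol 2.10 assigns Kaplan-Meier to the primary outcome, to estimate survival rates. It adds an intention-to-treat analysis of successes and failures, and Poisson regression on unspecified variables. For the groups: "For comparison between the two groups, Student's t test or Mann-Whitney test will be performed, depending on the normality of the data". It closes with "For all analyses, the significance value will be adjusted to 5" percent.
- **Intended claim.** Protocol section 3 expects to learn whether the treatments differ and also "whether Guedes-Pinto paste in the NIET technique will present equal or better clinical and radiographic results when compared to the CTZ paste".

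**The concern.** A non-inferiority conclusion needs one outcome, one time point and one interval or test set against the limit. Here each of the three is open.

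- **Outcome:** clinical success alone, or clinical plus radiographic success. Section 2.9 supports both.
- **Time point:** 1, 3 or 6 months. The planning time point, 12 months, is not a scheduled visit, so section 2.4 does not settle the matter.
- **Comparison:** Kaplan-Meier is named for estimation only. The t or Mann-Whitney test has no stated variable or visit, and neither it nor any other analysis is linked to the 15% limit.

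With 5% applied to each analysis, an analyst following the text could report any of several results as the trial's answer. Those results need not agree. In particular, a limit fixed in percentage points is easier to meet at a visit where few failures have yet occurred.

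**Working it through.** **Inputs from the protocol.** CTZ success 86.4%, so failure 13.6%; limit 15%, read here as 15 percentage points; visits at 1, 3 and 6 months; 60 teeth per group. The last follows from the protocol's own inflation: 38 × (1 + 0.20 + 0.40) = 60.8, in line with 60. How the 38 was obtained is a separate question and is not used here.

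**Assumptions, not in the protocol.** Teeth are independent and all 60 per group are evaluated. The 86.4% applies at 6 months. The failure timings and correlations are as given below.

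**1. Which result decides: the sections side by side**

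| Element | Where stated | Fixed? |
|---|---|---|
| Success definition | 2.9 text: clinical primary, radiographic secondary; 2.9 table: both required | No, two definitions |
| Visit | 2.9: 1, 3 and 6 months; 2.4: 12 months | No |
| Comparison with the 15% limit | 2.10: none of the listed analyses | No |
| Alpha | 2.4 and 2.10: 5%, sidedness not stated | Partly |

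**2. Tests of difference at three visits, one success outcome.** If the tests were independent, the chance of at least one false positive at 5% each is 1 − 0.95³ = 14.3%. Repeated visits on the same teeth are correlated. Simulating three equally correlated normal statistics at two-sided 5% gives:

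| Assumed correlation | At least one false positive |
|---|---|
| 0.3 | 13.6% |
| 0.5 | 12.5% |
| 0.8 | 9.9% |

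This is about two to three times the stated 5%.

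**3. The fixed limit at each visit.** Take a true 6-month failure of 13.6% for CTZ and 13.6 + 15 = 28.6% for Guedes-Pinto, so that the gap equals the limit. Assume one third of failures occur by month 1 and two thirds by month 3. The limit is met when the one-sided 95% Wald upper bound of the failure difference is below 0.15. Approximately,

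Pr(limit met) = Φ[(0.15 − d)/SE − 1.645], with SE = √{[p₁(1 − p₁) + p₂(1 − p₂)]/60}.

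| Visit | p₁ | p₂ | True gap d | SE | Approximation | Simulation |
|---|---|---|---|---|---|---|
| Month 1 | 0.045 | 0.095 | 0.05 | 0.0465 | Φ(2.15 − 1.645) = 69% | 70% |
| Month 3 | 0.091 | 0.191 | 0.10 | 0.0628 | Φ(0.80 − 1.645) = 20% | 22% |
| Month 6 | 0.136 | 0.286 | 0.15 | 0.0732 | Φ(0 − 1.645) = 5% | 6% |

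In the simulation the limit is met at one or more visits in 71% of trials.

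**4. Sensitivity to the assumed timing and alpha.** At one-sided 5%, the limit is met at one or more visits in 43% of trials if half of failures occur by month 1 and three quarters by month 3. The figure is 92% if one fifth occur by month 1 and half by month 3. At one-sided 2.5% the three timings give 31% to 87%. The size depends heavily on timing. In all three patterns the limit is easier to meet the earlier the visit.

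**The case against.** **The four signs are not four endpoints.** A reader might infer that each sign at each visit is a candidate primary test, twelve in all, and more with the radiographic signs. The documents do not support this. The table in 2.9 collapses the signs into one success or failure, since any sign rules out success. No test of a single sign is planned, and the radiographic signs are labelled secondary. The multiplicity that can be argued from the text is one success outcome at three visits, under two competing definitions.

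**Kaplan-Meier spans the visits.** This is true, and recording data at a visit is not a plan to test there. But Kaplan-Meier is named to estimate rates, without a between-group comparison or a reading time. It does not select the deciding contrast.

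**An early pass is not an error about that visit.** This stands. In the illustration the true gap at months 1 and 3 is 5 and 10 points, inside the limit. It would be wrong to call those passes false conclusions. They mislead only if they are presented as the answer on a paste that is worse by the full limit at 6 months.

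**The 10-14% is for tests of difference, while the design is non-inferiority.** This is also true. The figure applies to the t or Mann-Whitney comparison in 2.10 and the difference question in section 3. The month-by-month figures address the limit.

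**A statistical analysis plan, not available here, may hold a multiplicity procedure.** It may, and the lack of an alpha split or gatekeeping is not the complaint. The complaint is that the protocol's own sections conflict on the success definition and time point, and that its statistical section leaves the 15% limit unconnected to any comparison.

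**Conclusion.** The point holds as an undefined deciding contrast. The protocol sets a 15% limit but leaves the success definition, the visit and the comparison open, and it gives every analysis the same 5%. For one success outcome tested for a difference at three visits, the cost is a false-positive rate of about 10-14% instead of 5%, for correlations from 0.8 to 0.3. For the limit itself, a paste worse by the full 15 points at 6 months would meet it in about 70% of trials at month 1 and 22% at month 3, against 5-6% at month 6. Those last figures rest on the assumed failure timing, 60 independent evaluated teeth per group and one-sided 5%. They show the direction firmly and the size only roughly. Resolve this before analysis; it does not call the conduct of the trial into question.

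**What to change.** In 2.9 and 2.10:

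1. State one success definition for the primary outcome. Clinical success alone (none of the listed signs or symptoms) matches the label in 2.9; the radiographic criteria then become secondary, and the table should say so.
2. Name the between-paste difference in that success proportion at 6 months as the single deciding contrast. It may be a simple proportion or the Kaplan-Meier estimate at 6 months; choose one in advance.
3. State that its confidence bound is compared with the 15% limit, give the one-sided alpha, and say that the limit is in percentage points if that is meant.
4. Label the 1- and 3-month, radiographic and Poisson results as secondary or exploratory, reported as estimates with confidence intervals. Replace the blanket 5% sentence with this statement.
5. In 2.4, reconcile the 12-month planning rate with the 6-month end of follow-up.

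The cost is wording only: no extra teeth, visits or data. The small downside is that the early-visit, radiographic and regression results can no longer be presented as confirmatory.

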### 3. Expected Results

Through the present work, we will be able to assess whether there will be a difference in effectiveness between the proposed treatments, as well as whether Guedes-Pinto paste in the NIET technique will present equal or better clinical and radiographic results when compared to the CTZ paste.

## 4. Execution Schedule

[illegible]

